## Abstract

**Background:**

Although many efforts have been made to decrease the incidence of anastomotic leak (AL), it remains one of the most serious complications of rectal cancer surgery. Many previous studies have reported an association between the ligation level of the inferior mesenteric artery (IMA) (high or low) and the incidence of AL after rectal cancer surgery. However, we cannot draw a solid conclusion because of the low quality and heterogeneity of those studies. Therefore, this study aims to investigate the impact of the IMA ligation level on the occurrence of AL after minimally invasive anterior resection of rectal cancer.

**Methods/design:**

Patients with primary rectal cancer without distant metastases will be included after screening. They will be randomly assigned (1:1) to receive high or low ligation of the IMA. The primary endpoint is AL incidence; secondary endpoints are quality of life; urinary, sexual, and defecatory functions; and 3-year disease-free survival. We hypothesized that the incidence rate of AL would be 15% and 5% in the high- and low-ligation groups, respectively. With a two-sided *α* of 0.05 and a power of 0.8, the sample size is calculated to be 314 patients (157 per group), considering a 10% dropout rate.

**Discussion:**

Although many studies have compared the short- and long-term outcomes of high and low ligation of the IMA in rectal cancer surgery, it is still debatable. This trial aims to help draw a more solid conclusion regarding the association between the IMA ligation level and AL incidence after rectal cancer surgery. We also hope to contribute to standardizing the method of rectal cancer surgery in this trial.

**Trial registration:**

Clinical Research Information Service KCT0003523. Registered on February 18, 2019

**Supplementary Information:**

The online version contains supplementary material available at 10.1186/s13063-022-06862-0.

## Background

Surgical treatment of rectal cancer has developed significantly over several decades. The introduction of total mesorectal excision (TME) has dramatically improved the oncologic outcomes of rectal cancer [1], and organ-preserving surgery, such as intersphincteric resection, has been developed [2]. Recently, laparoscopic surgery has been widely performed for the management of rectal cancer [3], and transanal TME has been studied as a new method of rectal cancer surgery [4]. These surgical methods have been developed based on an increasing understanding of the rectal anatomy.

However, the level of ligation of the inferior mesenteric artery (IMA) in rectal cancer surgery is an old debate. The IMA can be ligated at the level of its root (high ligation, HL) or below the origin of the left colic artery (LCA) (low ligation, LL) [5]. The ligation level may be associated with several important issues, such as anastomotic leak (AL) and oncologic and functional outcomes of rectal cancer surgery [6, 7]. One of the major concerns regarding LL is that the apical lymph nodes (LNs) around the IMA may remain, which can affect survival outcomes [8]. Recent meta-analyses showed that the number of harvested LNs is similar between HL and LL [6, 7]. In addition, survival outcomes also show no difference between HL and LL [6, 7]. In fact, many surgeons perform apical LN dissection when performing LL; therefore, assuming that LN dissection has been properly performed, it is unlikely that LL will significantly impact the oncologic outcomes. The functional outcome is also a very important issue regarding the level of IMA ligation. The bilateral trunks of the inferior mesenteric plexus pass through the root of the IMA [9]; therefore, HL of the IMA carries a higher risk of damage to the surrounding autonomic nerve plexuses, which may lead to postoperative genitourinary dysfunction [10]. A recent meta-analysis reported that urinary, defecatory, and sexual dysfunctions occurred less frequently after LL than after HL [6].

The most debatable issue regarding HL and LL is the occurrence of AL. The researchers in this study previously reported the risk factors and preventive measures for AL after rectal cancer surgery [11–13]. Despite efforts to decrease the incidence of AL, it remains one of the most significant concerns after rectal cancer surgery. If the IMA is ligated at a high level, impaired perfusion to the neorectum may result in an increased risk of AL [14]. Although a number of previous studies have reported a relationship between the level of ligation of the IMA and the incidence of AL, the relationship remains controversial [6, 7]. Some studies have reported that HL is associated with a higher incidence of AL [6, 15], whereas others have reported no difference in AL between HL and LL [10, 16]. There have been a few randomized controlled trials (RCTs) on this issue [10, 16–20], but most have a significant bias due to their low quality and small sample size [7]. In addition, studies designed with AL as the primary endpoint are even rarer [16].

Therefore, we designed this RCT to investigate the impact of the level of IMA ligation on AL and functional and oncologic outcomes in rectal cancer surgery.

## Methods/design

### Study design

This multicentre, prospective, randomized clinical trial will be conducted in nine tertiary hospitals in Korea. It is a superiority trial involving two parallel groups with a 1:1 allocation ratio. The study protocol is written per the Standard Protocol Items: Recommendations for Interventional Trials (SPIRIT) checklist [21].

### Objectives and hypotheses of the study

The primary objective of this study is to investigate the impact of the IMA ligation level on the incidence of AL after minimally invasive anterior resection of rectal cancer. As secondary objectives, the study will also assess the relationship between the level of IMA ligation and quality of life; urinary, sexual, and defecatory functions; and 3-year disease-free survival.

### Study participants

We will enrol patients with primary rectal cancer who are scheduled to undergo minimally invasive (laparoscopic or robotic) surgery regardless of whether they have received preoperative chemoradiotherapy. Eligible patients will be recruited from an outpatient clinic before surgery. The investigator will take sufficient time to provide adequate study information to eligible patients regarding the study objectives, interventions, potential risks and benefits, and their rights. Patients will read and sign an informed consent form. We will request consent for the review of participants’ medical records and for the collection of blood samples to assess recurrence. Even if patients decline to participate in the study, their treatment will not be affected. Patients have the right to withdraw at any time if they wish.

The inclusion criteria will consist of patients with clinical stage I–III primary rectal cancer (within 15 cm from the anal verge), aged 18–80 years, who are eligible for laparoscopic surgery, and who have provided written consent to participate in the study. The exclusion criteria will consist of patients with stage IV disease; patients who are scheduled to undergo intersphincteric or abdominoperineal resection; patients with familial adenomatous polyposis or inflammatory bowel disease; patients with intestinal obstruction or perforation; patients with other malignancies, including synchronous colon cancer; and patients with serious underlying diseases who are judged to be inappropriate to participate. All enrolled patients will be randomized in a 1:1 ratio into the HL or LL arm (Fig. 1).

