### Surgical interventions

All participating surgeons had more than 5 years of experience contributing to colorectal surgery and performed at least 50 laparoscopic or robotic rectal cancer surgeries. The first case of the participating surgeon will be released to the other surgeons as an unedited video and discussed to maintain the quality of the surgery.

All patients will undergo minimally invasive (laparoscopic or robotic) surgery according to the oncologic principle of no-touch isolation. After careful inspection of the entire abdomen, the peritoneum will be opened from the presacral space and will proceed upwards. In the HL group, the IMA will be identified and ligated 2 cm from its origin. In the LL group, the LCA will be identified and preserved, and the IMA will be ligated immediately below the origin of the LCA. The apical LNs along the superior aspect of the IMA will be dissected while saving the IMA [22]. In both groups, at the surgeon’s discretion, the inferior mesenteric vein will be ligated and divided at the inferior border of the pancreas or at a similar level of IMA ligation. The hypogastric nerve and the left ureter will be carefully identified and preserved. The surgeon will determine the extent of splenic flexure colon mobilization. Intraoperative angiography with indocyanine green will be performed at the surgeon’s discretion. After TME or tumour-specific mesorectal excision according to the tumour’s location, double-stapling anastomosis will be performed. Diverting ileostomy will be performed in selected patients, as determined by the surgeon. The detailed surgical method is presented in a video clip (Additional file 1: Supplementary Video).

Implementing HL or LL will not require alterations to the usual care pathways (including the use of any medication), and such treatments will continue for both trial arms.

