### Sample size calculation

Based on previously published studies, we hypothesized that the rate of AL would be 15% and 5% in the HL and LL groups, respectively. With a two-sided *α* of 0.05 and a power of 0.8, the sample size was calculated as 314 patients (157 per group), considering an estimated dropout rate of 10%. The formula used to calculate the sample size is as follows:$$n=\frac{{\left({z}_{\alpha }+{z}_{\beta /2}\right)}^2}{{\left(\delta -|\varepsilon |\right)}^2}\left[\frac{p_1\left(1-{p}_1\right)}{k}+{p}_2\left(1-{p}_2\right)\right]$$

(*α* = alpha; *β* = 1 − power; *ε* = *p*_1_ − *p*_2_; *δ* = noninferiority margin; *n*_1_ = *kn*_2_)

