### Randomization

Random allocation will be performed in a 1:1 ratio using the permuted block technique, stratified by gender and preoperative chemoradiotherapy. The randomization sequence will be generated independently by the study statistician before being provided to the randomization contact for onward use. After enrolling patients, the investigators will contact the research coordinator of the initiating institution (School of Medicine, Kyungpook National University) via telephone on the day before the surgery, and they will be able to know which group the registered patient is assigned to.

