### Statistical analysis

We will analyse the data using two analysis sets: the intention-to-treat set, considering all patients as randomized regardless of whether they underwent the randomized surgical intervention, and the per-protocol set. Considering that there will be very few patients expected to crossover, these analyses should be very closely matched. Because symptomatic AL will be evaluated during hospitalization after surgery, we expect no missing data on the primary outcome. For other missing data, we will utilize multiple imputation under the assumption of missing at random.

Categorical variables will be compared using the *χ*^2^ or Fisher’s exact test, and continuous variables will be compared using Student’s *t*-test or the Mann–Whitney *U*-test. Disease-free survival will be measured from the date of surgery to the date of recurrence or death. Survival rates will be estimated and compared using the Kaplan–Meier method and log-rank test, and the Cox proportional hazard model will be utilized for multivariable survival analysis. Subgroup analyses will be conducted for each randomization stratum. All variables with a *p*-value < 0.05 will be considered significant. All statistical analyses will be performed using SPSS 27.0 (IBM Inc., Armonk, NY, USA).

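### The primary leak comparison is a crude test that ignores both randomisation factors and tumour height, giving up a little precision that a change of wording could recover

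*Protocol article*

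**What the plan says.** All references are to the protocol article.

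- **Study participants:** eligible tumours lie "within 15 cm from the anal verge". Patients scheduled for intersphincteric or abdominoperineal resection are excluded.
- **Surgical interventions:** the type of excision follows tumour location. The sentence opens "After TME or tumour-specific mesorectal excision according to the" and goes on to name the tumour's site. Every patient then has a double-stapled anastomosis.
- **Randomization:** permuted blocks, "stratified by gender and preoperative chemoradiotherapy". Tumour height is not a factor.
- **Statistical analysis:** categorical variables are compared by a chi-square or Fisher's exact test, with no covariate named. The only multivariable model is a Cox model for survival. On subgroups: "Subgroup analyses will be conducted for each randomization stratum".
- **Sample size calculation:** the design assumption is that "the rate of AL would be 15% and 5% in the HL and LL groups, respectively". The type I error is 5%, two-sided, the target power is 80%, and the size is inflated for 10% dropout, giving 157 per group.

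**The concern.** Distance from the anal verge has to be known before randomisation, because eligibility turns on it, and by the protocol's own text tumour location decides which excision is done. The primary outcome is a leak at the anastomosis that results, pooled over these operations. Gender and preoperative chemoradiotherapy were thought important enough to stratify on. The stated primary comparison uses none of the three.

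If any of them predicts leak, an adjusted analysis is somewhat more precise than the crude one. It also removes the part of the estimate that is due to chance imbalance in height, which the randomisation does not control. With few expected events, small gains have some value. If no adjustment is fixed in advance, adjusting later because height turned out imbalanced would be open to the charge of being post hoc.

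**Working it through.** **1. The plan's own figure.** Inputs from Sample size calculation: 15% and 5%, two-sided alpha 0.05, power 0.80, dropout 10%. Using the pooled two-proportion formula without continuity correction, the mean rate is 0.10 and

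n = [1.960 × √(2 × 0.10 × 0.90) + 0.842 × √(0.15 × 0.85 + 0.05 × 0.95)]² / 0.10² = (0.8315 + 0.3521)² / 0.01 ≈ 140.1, so 141 per arm.

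141 / 0.9 = 156.7, so 157 per arm and 314 in total. This matches the plan. Approximate power at 141 per arm is 80.3%. The planned size therefore rests on the crude test and does not need adjustment.

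**2. Expected events.** 141 × 0.15 + 141 × 0.05 = 21.15 + 7.05, about 28 leaks.

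**3. Gain from height alone.** The article gives no leak risk by height, so this step rests on assumptions: height is low or high, the low share is 30% or 50%, the odds ratio for leak (low against high) is 1, 2, 3 or 5, and the arm rates stay at 15% and 5%. The crude chi-square was compared with a Mantel-Haenszel test on two height strata, with 200,000 simulated trials per setting.

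| Odds ratio | Power at 141 per arm, crude | Power at 141 per arm, height-adjusted | Fall in variance of risk difference | Equivalent patients of 314 |
|---|---|---|---|---|
| 1 | about 81.7% | 81.7–81.8% | 0 | 0 |
| 2 | about 81.7% | 82.2% | about 1.0% | about 3 |
| 3 | about 81.8% | 82.9% | 2.3–2.7% | 7–9 |
| 5 | about 81.7% | 83.5–83.9% | 4.3–5.9% | 14–18 |

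At 157 per arm, power goes from about 86% to 86.2–86.3%, 86.6–86.8% and 87.2–87.8% for odds ratios 2, 3 and 5.

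The variance reduction is ½ × Var(p_HL(x) + p_LL(x)) / (0.15 × 0.85 + 0.05 × 0.95), where x is height. For example, at odds ratio 3 with half the tumours low, the stratum leak rates are 8.4% and 21.6% under high ligation and 2.6% and 7.4% under low ligation. The sums are 0.110 and 0.290, their variance is 0.09² = 0.0081, and ½ × 0.0081 / 0.175 = 2.3%.

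**4. Chance imbalance.** With half the tumours low and 157 per arm, the standard error of the difference in low share is √(0.25 × 2 / 157) = 0.056. A difference of 10 points or more in either direction then has probability about 0.076. At a risk ratio of 3 and a mean leak rate of 10%, low and high tumours leak at about 15% and 5%. A 10-point imbalance would move the leak difference by 0.10 × (15 − 5) = 1 point, against a target of 10.

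**5. Which adjusted analysis.** Crossing gender, chemoradiotherapy and a binary height gives 2 × 2 × 2 = 8 strata, with about 7 expected leaks in the low-ligation arm to spread over them. Simulation assumed 60% men, 40% chemoradiotherapy, and both factors unrelated to height and to leak (100,000 trials per setting, 141 per arm). Crude power was 81.4–81.9%. The eight-stratum Mantel-Haenszel test gave 81.1–81.3% at ratio 2, 82.0% at ratio 3 and 83.0–83.6% at ratio 5. A main-effects logistic model, with half the tumours low and the strata again not prognostic, gave 83.0% against 82.3% for the unadjusted likelihood-ratio test at ratio 2, and 84.4% against 82.6% at ratio 5. Within simulation error, the logistic model does at least as well as no adjustment. The eight-stratum test loses slightly at ratio 2.

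**The case against.** The strongest reply is that there is no error here. A crude test after randomisation is valid, chance imbalance in height is already covered by its type I error, and the stated sample size reproduces without adjustment. All of that stands. A reader might infer that the crude comparison is biased or that the trial is underpowered for want of adjustment; the documents support neither.

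Nothing in the article says that height predicts leak, so the size of the gain is wholly assumed and could be zero. This also stands. Nor is the mix of tumours as wide as the 15 cm limit alone suggests: planned intersphincteric and abdominoperineal resections are excluded, and participation ends if surgery finishes that way or is converted to open. A reader might also take it that height is already in the data set. That is an inference from the eligibility criterion and the preoperative work-up (digital rectal examination, colonoscopy, imaging); the article does not list height as a recorded variable.

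Crossing all three factors in a Mantel-Haenszel test gains little or nothing at modest ratios. That objection is right against that method, but not against a main-effects model.

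Finally, covariate adjustment is often left to a statistical analysis plan, which is not at hand and may already provide it. That limits the point to the comparison the article does state. It is no charge of omission.

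**Conclusion.** The point holds as a low-severity improvement to the analysis. The stated primary comparison leaves out two factors used in the randomisation and a baseline value that must be known for eligibility and that bears on the operation. The price is small: about 0.5 to 2 power points from height at 141 per arm, or 1 to 6% of the variance of the risk difference, if the odds of leak in low tumours are 2 to 5 times those in high ones and 30 to 50% of tumours are low. With no relation between height and leak, the price is nil. Any gain from gender and chemoradiotherapy depends on how far they predict leak, which the article does not say. Larger gains should not be claimed. The absence of height from the stratification is not itself a fault, and recruitment has been under way since April 2019.

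**What to change.** In Statistical analysis, prespecify the primary intention-to-treat comparison of leak as a main-effects logistic model with arm, gender, preoperative chemoradiotherapy and baseline tumour distance from the anal verge (linear in cm, or one cut fixed in advance). Report it as a marginal risk difference with its confidence interval, and keep the crude chi-square as supportive. Name the test of the arm term in advance, and do not use a fully cross-classified eight-stratum Mantel-Haenszel test. Confirm that tumour distance is recorded on the case report form before randomisation. If a separate analysis plan already adjusts, bring the two texts into line.

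The cost is wording: randomisation, sample size and patient care are untouched. The downside is four model terms on about 28 expected leaks, and a model-based estimate that needs a sentence of explanation. The change should be made before the data are unblinded to the analysts.

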**Fig. 1 Fig1:**
[figure not shown]
Flow chart

### Surgical interventions

All participating surgeons had more than 5 years of experience contributing to colorectal surgery and performed at least 50 laparoscopic or robotic rectal cancer surgeries. The first case of the participating surgeon will be released to the other surgeons as an unedited video and discussed to maintain the quality of the surgery.

All patients will undergo minimally invasive (laparoscopic or robotic) surgery according to the oncologic principle of no-touch isolation. After careful inspection of the entire abdomen, the peritoneum will be opened from the presacral space and will proceed upwards. In the HL group, the IMA will be identified and ligated 2 cm from its origin. In the LL group, the LCA will be identified and preserved, and the IMA will be ligated immediately below the origin of the LCA. The apical LNs along the superior aspect of the IMA will be dissected while saving the IMA [22]. In both groups, at the surgeon’s discretion, the inferior mesenteric vein will be ligated and divided at the inferior border of the pancreas or at a similar level of IMA ligation. The hypogastric nerve and the left ureter will be carefully identified and preserved. The surgeon will determine the extent of splenic flexure colon mobilization. Intraoperative angiography with indocyanine green will be performed at the surgeon’s discretion. After TME or tumour-specific mesorectal excision according to the tumour’s location, double-stapling anastomosis will be performed. Diverting ileostomy will be performed in selected patients, as determined by the surgeon. The detailed surgical method is presented in a video clip (Additional file 1: Supplementary Video).

Implementing HL or LL will not require alterations to the usual care pathways (including the use of any medication), and such treatments will continue for both trial arms.

### Criteria for discontinuing or modifying allocated interventions

LL can be converted to HL if there is an inevitable reason, such as securing a sufficient colon length to perform the anastomosis. Participation will be discontinued when surgery is completed with intersphincteric resection, abdominoperineal resection, or conversion to open surgery. If the investigators fail to perform the allocated interventions, the reason will be recorded in the medical record.

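### The rule ending participation after certain surgical endings conflicts with the promised all-randomised analysis and opens the leak comparison to selection bias of unknown size and direction

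*Protocol article*

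**What the plan says.** Under Criteria for discontinuing or modifying allocated interventions, the protocol article states: "Participation will be discontinued when surgery is completed with intersphincteric resection, abdominoperineal resection, or conversion to open surgery". Planned intersphincteric and abdominoperineal resections are already excluded at entry (Study participants), so for those two operations the rule acts on changes made at surgery. Open conversion is by nature an event during surgery.

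The order of events follows from two other sections. Under Randomization, investigators learn the allocation "via telephone on the day before the surgery, and they will be able to know which group the registered patient is assigned to". Under Blinding, the surgeon is not blinded and is also the assessor of symptomatic AL.

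The Statistical analysis section describes "the intention-to-treat set, considering all patients as randomized regardless of whether they underwent the randomized surgical intervention". Of AL it says "we expect no missing data on the primary outcome", because AL is evaluated during the hospital stay. Imputation is reserved for the rest: "For other missing data, we will utilize multiple imputation under the assumption of missing at random". Nothing in the article says whether AL is still recorded for a patient whose participation has ended, or how that patient enters the intention-to-treat set.

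**The concern.** The discontinuation rule selects patients on something that happens after randomisation and after an unblinded surgeon has acted on the allocation. The analysis set is meant to contain everyone randomised. If participation ends in the ordinary sense of the word, some members of that set have no primary outcome. The plan has no rule for them, because it expects none to be missing and limits imputation to other data.

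This matters because the patients concerned are unlikely to be a random sample. An operation that ends in open conversion or intersphincteric resection may still leave an anastomosis that can leak, and leak risk there may differ from the trial average. An abdominoperineal resection leaves no anastomosis at all. If such endings are more frequent in one arm, dropping them changes that arm's AL rate for reasons unrelated to the effect of ligation level. The same patients would be lost to 3-year disease-free survival and the questionnaires if the end of participation also ends follow-up.

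**Working it through.** **Setting the sections side by side.**
- Allocation is disclosed the day before surgery. The triggering event occurs at surgery, so the removal comes after randomisation.
- The person whose decisions determine the ending knows the arm and later judges AL.
- The intention-to-treat set includes all patients as randomised. The explicit extension covers patients who did not receive the allocated ligation. It does not mention patients whose participation was ended.
- AL is recorded within 1 month after surgery (Assessment of outcomes), which is after the triggering event.

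So either AL is still recorded for these patients, which the article does not say, or the set has missing primary outcomes, which the article says it does not expect.

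**The plan's own figure.** Inputs from Sample size calculation: AL 15% v 5%, two-sided alpha 0.05, power 0.80, 10% dropout. With the pooled-variance formula, n = [1.960 × √(2 × 0.10 × 0.90) + 0.842 × √(0.15 × 0.85 + 0.05 × 0.95)]² / 0.10² = (0.8315 + 0.3521)² / 0.01 = 140.1, so 141 per group. Then 141 / 0.9 = 156.7, so 157 per group and 314 in total, as stated. Power is 0.843 if all 157 per group are analysed and 0.803 if 10% leave each arm. Loss of power is therefore minor, and the issue is bias.

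**Size of the bias.** The documents give no discontinuation rate and no leak rate among discontinued patients, so what follows is assumed. Let the true AL rate be 10% in both arms, d the share of an arm removed, and q the AL rate among those removed. The AL rate in the patients who remain is

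r = (0.10 − d × q) / (1 − d).

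The type I error is the exact rejection probability of the two-sided Pearson chi-square test at 5%, using the remaining patients. It is 5.1% with nobody removed.

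| Removed HL / LL | q | r in HL | r in LL | Spurious difference | Patients HL / LL | Type I error |
|---|---|---|---|---|---|---|
| 5% / 5% | 20% | 9.47% | 9.47% | none | 149 / 149 | 4.9% |
| 5% / 10% | 20% | 9.47% | 8.89% | 0.6 points favouring LL | 149 / 141 | 5.4% |
| 5% / 10% | 30% | 8.95% | 7.78% | 1.2 points favouring LL | 149 / 141 | 6.5% |
| 5% / 15% | 30% | 8.95% | 6.47% | 2.5 points favouring LL | 149 / 133 | about 11.5% |
| 5% / 15% | 0% | 10.53% | 11.76% | 1.2 points against LL | 149 / 133 | 6.3% |

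For example, in the fourth row: HL (0.10 − 0.05 × 0.30) / 0.95 = 0.0895; LL (0.10 − 0.15 × 0.30) / 0.85 = 0.0647; the difference is 0.0248.

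The last row shows why direction cannot be assumed. If those removed have no anastomosis, as after abdominoperineal resection, q is zero and the sign reverses. Exchanging the arms would also reverse every row.

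**The case against.** The strongest reply is that the all-randomised analysis remains possible. The rule stands under a heading about discontinuing or modifying interventions, AL is evaluated during the hospital stay, and patients consent to review of their medical records. AL could therefore be obtained for discontinued patients, and the full protocol, which is not shown, may require it. This stands in part. A reader might infer that an intention-to-treat analysis cannot be done, or that these patients certainly leave oncologic follow-up; the article supports neither as a fact. What it does contain is a sentence that ends participation, beside an analysis set that needs these patients' outcomes, with nothing to connect the two.

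Three further inferences are tempting and not supported.
- That a shorter colon makes these endings more frequent under LL. The article ties colon length to a change of ligation level ("LL can be converted to HL if there is an inevitable reason, such as securing a sufficient colon length"), which is a crossover and does not end participation. Nothing links ligation level to open conversion, intersphincteric resection or abdominoperineal resection.
- That the 10% dropout allowance measures these endings or contradicts the analysis section. It is a planning margin, and the article does not attribute it to them.
- That the per-protocol set excludes patients from one arm only, or that the lack of a named primary set is an error. The article does not define the per-protocol set, and both matters are commonly left to the full protocol or SAP.

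It is also fair to say that the largest figure in the table needs a threefold imbalance between arms together with a threefold leak risk among those removed. The milder case of 5% v 10% with 20% leak moves the type I error only from 5.1% to 5.4%.

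**Conclusion.** The concern holds as a conflict between two stated rules. One section ends the participation of randomised patients on the basis of events during surgery, while another promises a set of all randomised patients, expects no missing AL data and has no rule for those patients. Because the surgeon is unblinded and assesses AL, removals that differ by arm are possible.

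The size and direction of any bias are unknown. Under the assumed rates, the spurious difference ranges from 1.2 points against LL to 2.5 points in favour of LL, compared with a planned difference of 10 points. The upper end rests on demanding assumptions, and rare, balanced removals would be harmless. These figures are illustrations of what the rule permits, not estimates for this trial. The conflict nevertheless deserves correction during the trial, because a later analysis plan may be unable to recover outcomes that were never collected.

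**What to change.** Reconcile the two sections with text along these lines:
- Patients whose operation ends as intersphincteric resection, abdominoperineal resection or open conversion remain in follow-up for AL, questionnaires and disease-free survival, and are analysed in their randomised arm.
- State how patients left without an anastomosis are counted. One option is to count them as no AL, with a sensitivity analysis excluding them. The sensitivity analysis is needed because an arm with more such patients would otherwise appear to leak less.
- Report the number of each ending by arm.
- Let these endings affect only the per-protocol set.
- Remove or qualify the statement that no primary outcome data will be missing.

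This concerns follow-up and analysis only and leaves surgical care as it is. The cost is an amendment approved by the IRB of each of the nine hospitals, and retrieval of outcomes for patients already discontinued since recruitment began in April 2019, possibly with renewed contact. The estimate will be slightly diluted by patients whose surgery did not go as planned. The sample size stays at 314.
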